**3) Subcutaneous Drainage Experimental Group**

Jackson-Pratt drain, 7 Fr (Manufacturer to be determined)

**4) Subcutaneous Drainage Control Group :** N/A

1. **Subject Eligibility and Exclusion Criteria, Target Sample Size and Calculation Rationale**
2. **Inclusion Criteria**

(1) Female patients planning to undergo elective midline laparotomy for gynecological diseases.

(2) Over 18 years old.

(3) ECOG performance status 0 - 2

1. **Exclusion Criteria**

(1) Patients with previous or present abdominal incisional hernia.

(2) Pregnant patients.

(3) Patients receiving external radiation treatment to the pelvis or abdomen.

(4) Patients allergic to PDS components.

(5) Patient with diseases that affect wound healing including uncontrolled diabetes, autoimmune vasculitis, and hepatocirrhosis.

(6) BMI>35

(7) Patients are excluded if they have used or are expected to use drugs that may affect wound healing such as bevacizumab. In case where bevacizumab is used, participation is possible if they have a four-week washout period before and after surgery, respectively.

(8) Patients who have had an abdominal midline laparotomy for the last 6 months.

(9) If patients had surgery for suspected infection.

1. **Target Sample Size and Calculation Rationale**

(1) Previous study results were referenced to assume 1-year cumulative incidence of incisional hernia as 0.13 in SS-PDS control group (C+D arm) [PMID: 26188742].

(2) No previous studies have investigated the incidence of incisional hernia after using barbed suture for abdominal fascia closure. Given that there are cases of very low incisional hernia incidence such as 1-2% in previous studies using conventional closure methods, 1-year cumulative incidence of incisional hernia in SS-PDS experimental group (A+B arm) is estimated to be 0.03.

(3) Alpha 0.05 (one-sided), power 0.8, drop-out rate 0.06, each arm (A+B vs C+D): 87 patients

(4) Therefore, the target sample size is 174.

1. **Recruitment Plan**

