B. Reasons for selection

A) Fascia closure of abdominal midline incision has been developed from interrupted sutures to continuous running sutures using monofilament sutures. In recent randomization studies, suture techniques that include less tissues were found to reduce the incisional hernia incidence. [PMID: 20395846,12594682, 26188742, 19917943].

B) The European Hernia Society recommends using sutures with delayed absorption, and this is accepted as a standard [PMID: 25618025].

C) 2 meta-analyses compared sutures with delayed absorption were compared and non-absorbent sutures. While sutures with delayed absorption had similar incisional hernia with non-absorbent sutures, suture sinus and wound pain were reduced. Use of sutures with delayed absorption is recommended for this reason [PMID: 20395846, 22061310].

D) When sutures with delayed absorption were compared to sutures with rapid absorption in a recent meta-analysis, less incisional hernia was associated with sutures with delayed absorption [PMID: 20395846]

(3) Subcutaneous drain experimental group (subcutaneous drain is inserted)

A. Instructions

A) Device: Jackson-Pratt drain, 7 Fr (manufacturer to be determined)

B) Place closed, negative drain at hypodermis. The drain should be inserted through a skin perforation separate from the surgical incision.

C) Subcutaneous tissue closure is not necessary, but can be performed based on the investigator’s judgment.

D) Skin closure can be performed using stapler or non-absorbent sutures whichever is a general method of each institution.

E) Based on the investigator’s judgment, the subcutaneous drain can be removed any time between 3 days and 14 days after operation when the drainage volume is less than 10cc. If daily drainage volume is greater than 10cc until when the applicable patient is discharged, the subcutaneous drain can be removed based on the investigator’s judgment. If daily drainage volume is greater than 10cc when 14 days have passed after surgery, the subcutaneous drain can be maintained or removed based on the investigator’s judgment.

F) In case it is impossible to insert subcutaneous drain because the subcutaneous layer is too thin, the drain may not be inserted based on the investigator’s judgment.

B. Reasons for selection

The reasons are stated under the section ‘Background.’

(4) Subcutaneous control group (subcutaneous drain is not inserted)

A. Instructions

1. Subcutaneous drain is not inserted.

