2. Subcutaneous tissue closure is not necessary, but can be performed based on the investigator’s judgment.

3. Skin closure can be performed using stapler or non-absorbent sutures whichever is a general method of each institution.

B. Reasons for the choice

The reasons are stated under the section ‘Background.’

1. **Observation Items, Clinical Test Items, Observation and Test Methods**

| Observation Items | Observation and Test Methods |
| --- | --- |
| 1-year cumulative incidence of incisional hernia after surgery | Subjects are advised to make outpatient visits for Year 1 after surgery. Visits made between 9 and 15 months after surgery can be counted as Year 1 visit. Investigators will conduct a physical checkup to diagnose incisional hernia. Investigators can refer to post-surgery image test result. If investigators are not sure of incisional hernia, a diagnostic test can be carried out. Subjects will be censored if they underwent midline laparotomy once again after receiving the surgery from this study, are dead or lost to follow-up at the time of event. Investigators will not be reminded of group allocation and will be blinded until Year 1 visit is completed. |
| 4-week cumulative incidence and types of surgical site infection after surgery | Subjects are advised to make outpatient visits for Week 4 after surgery. Visits made between 3 to 5 weeks after surgery can be counted as Week 4 visit. Investigators will conduct a physical checkup to diagnose surgical site infection. If subjects make outpatient visits before Week 4 after surgery, investigators should check for surgical site infections and their types. All information obtained from visits made immediately after surgery up to Week 4 will be used to diagnose all surgical site infections. CDC standards will be used to determine surgical site infections and their types. (https://www.cdc.gov/nhsn/PDFs/pscManual/17pscNosInfDef_current.pdf). If any surgical site infection is observed according to CDC standards, the patient will be judged to have a surgical site infection. Investigators will not be reminded of group allocation. |

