| 4-week cumulative incidence of wound dehiscence after surgery | Subjects are advised to make outpatient visits for Week 4 after surgery. Visits made between 3 to 5 weeks after surgery can be counted as Week 4 visit. Investigators will conduct a physical checkup to diagnose wound dehiscence. Wound dehiscence is defined as all wound dehiscence in any depth and length. If subjects make outpatient visits before Week 4 after surgery, investigators should check for wound dehiscence. All information obtained from visits made immediately after surgery up to Week 4 will be used to calculate all cumulative incidence. Events that will be included in the calculation of cumulative incidence will be: when wound dehiscence is observed even just once until Week 4 after surgery; when removal of stapler or suture is impossible at Week 4; or wound dehiscence is observed during follow-up after stapler or suture was removed at Week 4. |
| Wound dehiscence incidence at week 4 after surgery | Subjects are advised to make outpatient visits for Week 4 after surgery. Visits made between 3 to 5 weeks after surgery can be counted as Week 4 visit. Investigators will conduct a physical checkup to diagnose wound dehiscence. Wound dehiscence at Week 4 is defined as: when a wound is expanded at Week 4 evaluation; when removal of stapler or suture is impossible; or wound dehiscence is observed during follow-up after stapler or suture was removed at Week 4. If wound dehiscence was observed before Week 4 but it disappeared at Week 4, the subject is not counted to have wound dehiscence at Week 4 after surgery. When stapler or suture is removed at Week 4 visit, a follow-up visit or phone counseling is required. If no wound dehiscence is discovered from the follow-up visit or phone counseling, the subject is not counted to have wound dehiscence. However, if wound dehiscence is discovered from the follow-up visit or phone counseling, the subject is counted to have wound dehiscence. |
| BPI-K Score | BPI-Korean version is used at baseline, Day 2 and Day 4 after surgery. |
| NRS Pain Score | Pain scores, measured by NRS which is a usual way of monitoring surgical patients, and record times are collected from immediately after surgery until 10pm of Day 4 after surgery. |

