| Demographics of subjects, surgical information | Date of birth, height, weight, current smoker, medical history, pre- and postoperative chemotherapy, corticosteroids, previous abdominal surgery, ASA classification, type of surgery, suture length, wound length, operation time, antibiotic prophylaxis, intra-abdominal drain, subcutaneous drain, DVT prophylaxis, Patient controlled analgesia (Y/N, type IV or epidural), wound anesthetics infiltration system, perioperative complications, transfusion, postoperative radiation, ICU care |
| Incidence, types, grades and relevance of adverse events excluding incisional hernia, pains, surgical site infections, and wound dehiscence | Adverse events are collected by listening to the subject’s medical history and conducting a physical checkup during hospitalization for surgery, Week 4 and Year 1 visits after surgery. All visits and medical records until Year 1 after surgery will be used. CTCAE ver 4.0 will be used to grade each adverse event. |

1. **Efficacy Evaluation Standards, Evaluation Methods**

| Purpose | Analysis and Evaluation Methods | Cohorts for analysis |
| --- | --- | --- |
| Compare cumulative incisional hernia incidence until Year 1 after surgery between A+B arm and C+D arm. | Cumulative incidence of incisional hernia of A+B arm will be compared with that of C+D arm using chi-square or Fisher's exact test. P value 0.05 will be used to determine significance. | All patients who undergo surgery. Patients who do not have incisional hernia will be censored at last visit. Incidence will be estimated from time-occurrence curve. |
| Compare incisional hernia incidence curve by time between A+B arm and C+D arm. | Time-occurrence curve of incisional hernia will be depicted using Kaplan-Meier method and be compared between A+B vs C+D arm using log-rank test. P value 0.05 will be used to determine significance. | All patients who undergo surgery |
| Compare cumulative incidence of surgical site infections and their types until Week 4 after surgery between A+B arm and C+D arm. | Cumulative incidence of SSI of A+B arm will be compared with that of C+D arm using chi-square or Fisher's exact test. P value 0.05 will be used to determine significance. Type of SSI will be summarized. | Patients who undergo surgery |

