G) Infections and infestations: abdominal infection, bladder infection, catheter related infection, peritoneal infection, pharyngitis, stoma site infection, urinary tract infection, wound infection

H) Injury, poisoning and procedural complications: intraoperative gastrointestinal injury, intraoperative venous injury, intraoperative urinary injury, large intestinal anastomotic leak, postoperative hemorrhage, wound complication, wound dehiscence

I) Investigations: activated partial thromboplastin time prolonged, alanine aminotransferase increased, alkaline phosphatase increased, aspartate aminotransferase increased, platelet count decreased, urine output decreased, weight gain, weight loss

J) Metabolism and nutrition disorders: anorexia, dehydration

K) Musculoskeletal and connective tissue disorders: back pain, flank pain, myalgia, neck pain

L) Psychiatric disorders: anxiety, delirium, insomnia

M) Renal and urinary disorders: hematuria, proteinuria, urinary frequency, urinary incontinence, urinary retention, urinary urgency

N) Reproductive system and breast disorders: menorrhagia, irregular menstruation, pelvic pain, vaginal discharge, vaginal dryness, vaginal hemorrhage

O) Respiratory, thoracic and mediastinal disorders: atelectasis, cough, dyspnea, hypoxia, pleural effusion, sore throat

P) Skin and subcutaneous tissue disorders: alopecia, pruritus, purpura, urticarial

Q) Vascular disorders: flushing, hot flashes, phlebitis, thromboembolic event

B. Side effects/risks from using barbed suture and countermeasures

A) Side effects/risks

Barbed suture has been used for various soft-tissue closures since years ago. SS-PDS is approved to be used for abdominal fascia closure. However, there are little clinical experience of using SS-PDS for abdominal fascia closure. Potential side effects/risks would include increased incisional hernia, surgical site infections, wound dehiscence and pain but increase is not expected.

B) Countermeasures

When the 10th subject is allocated to the A+B arm and completes his/her week 4 visit, an evaluation will be performed on 10 subjects in A+B arm for surgical site infections, wound dehiscence and incidence, types and grades of other adverse events. Evaluation results will be reported to IRB. If incidence, types, and grades of adverse events are judged to exceed the usual range, possible measures including trial discontinuation will be considered.

C. Side effects/risks from using subcutaneous drain and countermeasures

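### The adverse-event exclusion of surgical site infection, wound dehiscence and pain has no time limit, so late cases have no clearly specified comparison between suture arms

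*Protocol*

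**What the plan says.** The section on observation items and test methods sets a separate window for each wound outcome.

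- **Surgical site infection:** "All information obtained from visits made immediately after surgery up to Week 4 will be used to diagnose all surgical site infections". The Week 4 visit may fall between 3 and 5 weeks.
- **Wound dehiscence:** "All information obtained from visits made immediately after surgery up to Week 4 will be used to calculate all cumulative incidence". A case also counts when "wound dehiscence is observed during follow-up after stapler or suture was removed at Week 4". No end date is given for that follow-up.
- **Pain:** BPI-K is taken at baseline, Day 2 and Day 4. NRS scores and their "record times are collected from immediately after surgery until 10pm of Day 4 after surgery".

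The adverse-event row of the same table is headed "Incidence, types, grades and relevance of adverse events excluding incisional hernia, pains, surgical site infections, and wound dehiscence". Its method cell relies on history and examination in hospital, at Week 4 and at Year 1, and on all visits and records to Year 1. Secondary objective I and the last row of the table under Efficacy Evaluation Standards, Evaluation Methods carry the same exclusion. None of the three places limits it in time.

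Under Benefits for and Risks to Subjects, the part on the barbed suture states: "Potential side effects/risks would include increased incisional hernia, surgical site infections, wound dehiscence and pain but increase is not expected". It adds that there is little clinical experience with this suture in abdominal fascia.

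**The concern.** Leaving endpoint events out of the adverse-event item is a sensible way to avoid counting them twice. That works for hernia, whose endpoint also runs to Year 1. For infection, dehiscence and pain, the endpoint closes and the exclusion continues. A wound infection at Week 8, or wound pain still present at Year 1, falls outside its endpoint and is also of a type that the adverse-event item sets aside.

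These are three of the four risks that the protocol itself attributes to the barbed suture. If sites follow the observation table literally, late cases may go unrecorded. A later analysis plan cannot recover data that were not collected. A report of no excess wound complications to one year would then rest on about four weeks of wound data and four days of pain data.

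**Working it through.** No figure in the protocol is in dispute. The check sets the provisions side by side.

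**Step 1: windows against the exclusion** (365-day year; days left = 365 minus the last day covered)

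| Event | Own endpoint ends | Excluded from adverse events to Year 1 | Named suture risk | Days left without an endpoint |
|---|---|---|---|---|
| Incisional hernia | Year 1 visit | yes | yes | none |
| Surgical site infection | Week 4 visit | yes | yes | 365 − 28 = 337 (92%); visit at Week 5: 365 − 35 = 330 (90%) |
| Wound dehiscence | Week 4, plus check after removal at that visit | yes | yes | as for infection, less any time covered by the check |
| Pain | Day 4 | yes | yes | 365 − 4 = 361 (99%) |

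Window and exclusion match only for hernia.

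**Step 2: follow one late event through the protocol.** Take a wound infection first seen at Week 8.

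1. *Infection endpoint:* closed at the Week 4 visit.
2. *Adverse-event item in the observation table:* an excluded type.
3. *Adverse-event row of the efficacy evaluation table:* the same exclusion.
4. *Safety Assessment in the overview:* compares adverse events between the suture groups without an exclusion, so on its wording the event belongs. It does not say how this fits with items 2 and 3.
5. *Safety section, (2) Evaluation Methods:* no exclusion, but it covers only events judged related to the suture, and as written it contrasts A+C with B+D. That is the drain comparison, not the suture comparison.
6. *Safety section, (3) Reporting Methods, annual collection:* covers all adverse events, but as a report to the ethics boards, not as a comparison between arms.
7. *Expedited reporting:* requires an event in the SS-PDS arm that is serious, causally related and unpredicted. The risk section already lists wound infection and wound dehiscence as predictable, so a late case may not qualify.

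Only item 4 offers a suture-arm comparison that could include the event, and it conflicts with items 2 and 3.

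**Step 3: is the type an adverse event at all?** The list of predictable events in the risk section includes pain, wound infection and wound dehiscence as adverse events that may be observed. The observation table removes them. The two places need to be reconciled.

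**Step 4: size.** The documents give no rate of late wound events. Purely as an assumption, if 2% to 5% of patients had one, 0.02 × 87 = 1.7 to 0.05 × 87 = 4.4 patients per suture group would be affected. This says nothing about a difference between the groups.

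**The case against.** The strongest reply is that the exclusion only prevents double counting and that no passage tells a site to discard a late infection. The overview's safety assessment, the comparison of suture-related events and the annual collection all lack the exclusion. Where causality is hard to judge, the protocol treats the event as related, which would bring many late wound events into the related-event comparison. Dehiscence also has its check beyond Week 4. In addition, a four-week wound window and a Day 4 pain window are legitimate choices, and the planned comparisons are labelled with those times.

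Much of this stands. A reader might infer that late cases are counted nowhere, or that sites are obliged to leave them out. The documents do not support either reading, because the provisions without the exclusion could capture them. What remains is that those provisions contradict the collection row, and the most detailed of them compares the drain groups. Ending the endpoints early is not the fault; the fault is that the exclusion does not end with them.

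Two supporting arguments add little. Exclusion criterion 7 allows bevacizumab where "participation is possible if they have a four-week washout period before and after surgery, respectively", roughly when the wound window closes, but this applies equally to both randomised arms. The rationale for the control suture notes that "suture sinus and wound pain were reduced", but that concerns delayed-absorption against non-absorbent material, while both arms here use PDS Plus products. Suture sinus is not on the exclusion list in any case.

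**Conclusion.** The point holds as a mismatch between the exclusion and the endpoint windows, together with conflicting recording instructions. Infection or dehiscence after the Week 4 assessment, and pain after Day 4, have no clearly specified comparison of A+B with C+D, although the protocol names all three as potential risks of the suture under test.

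The gap covers about 90% to 92% of the year for infection and dehiscence and 99% for pain. These are shares of time, not of risk. They assume a 365-day year and, for dehiscence, ignore the open-ended check after removal. The number of events affected is unknown.

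A reader might also infer that the trial's safety conclusion would be wrong. The documents do not show that, since they give no late-event rate and no expected difference between arms. The primary endpoint and the stated four-week and Day 4 comparisons are unaffected. This should be fixed, but it does not undermine the trial.

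**What to change.** - In secondary objective I, the adverse-event row of the observation table and the adverse-event row of the efficacy evaluation table, limit the exclusion to events already counted within their own endpoint window.
- State that surgical site infection or dehiscence first seen after the Week 4 assessment (including its check after staple or suture removal), and wound pain after Day 4, are recorded as adverse events with CTCAE grade and relevance until Year 1.
- Tabulate these late events by A+B against C+D.
- Reconcile these places with the overview's Safety Assessment, with the Evaluation Methods and Reporting Methods of the safety section (including the arms contrasted there), and with the list of predictable adverse events.

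The cost is protocol wording and eCRF guidance. The Year 1 history, examination and record review are already planned, so no visit or procedure is added. The downside is more adverse-event entries, probably most of them for pain soon after Day 4; recording the grade keeps these interpretable.

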| Compare cumulative wound dehiscence incidence at Week 4 after surgery between A+B arm and C+D arm. | Cumulative incidence of wound dehiscence of A+B arm will be compared with that of C+D arm using chi-square or Fisher's exact test. P value 0.05 will be used to determine significance. | Patients who undergo surgery and complete week 4 visit |
| Compare wound dehiscence incidence at Week 4 after surgery between A+B arm and C+D arm. | Incidence of wound dehiscence of A+B arm will be compared with that of C+D arm using chi-square or Fisher's exact test. P value 0.05 will be used to determine significance. | Patients who undergo surgery and complete week 4 visit |
| Compare BPI-K scores that are obtained at baseline, Day 2 and Day 4 after surgery between A+B arm and C+D arm. | BPI score (total and each question) obtained at baseline will be compared between A+B vs C+D arm. BPI score (total and each question) obtained at postoperative day 2 will be compared between A+B vs C+D arm. BPI score (total and each question) obtained at postoperative day 4 will be compared between A+B vs C+D arm. Student t-test will be used. P value 0.05 will be used to determine significance. If BPI score at baseline is imbalanced between arms, change of BPI score (from baseline to postoperative day 2, 4) will be compared. | Patient who undergo surgery and complete BPI |
| Compare NRS pain scores collected until Day 4 after surgery between A+B arm and C+D arm. | NRS collected for postoperative 4 days will be compared between A+B vs C+D arm using linear mixed model. P value 0.05 will be used to determine significance. | Patients who undergo surgery and NRS are measured |
| Compare cumulative incidence and types of surgical site infections until Day 4 after surgery between A+C arm and B+D arm (depending on whether subcutaneous drain is inserted or not) | Cumulative incidence of SSI of A+C arm will be compared with that of B+D arm using chi-square or Fisher's exact test. P value 0.05 will be used to determine significance. Type of SSI will be summarized. | Patients who undergo surgery |
| Compare cumulative wound dehiscence incidence at Week 4 after surgery between A+C arm and B+D arm (depending on whether subcutaneous drain is inserted or not) | Cumulative incidence of wound dehiscence of A+C arm will be compared with that of B+D arm using chi-square or Fisher's exact test. P value 0.05 will be used to determine significance. | Patients who undergo surgery and complete week 4 visit |

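### BPI-K pain scores: the planned t-test ignores the collected baseline, and the undefined change-score rule for baseline imbalance gives a biased comparison when it fires; baseline-adjusted ANCOVA should replace both

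*Protocol*

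**What the plan says.** The observation table (Observation Items, Clinical Test Items, Observation and Test Methods) sets the assessment times: "BPI-Korean version is used at baseline, Day 2 and Day 4 after surgery". A baseline value is therefore collected for the same instrument as the outcome.

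The BPI-K row under Efficacy Evaluation Standards, Evaluation Methods then fixes four things:

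- A between-arm comparison at baseline: "BPI score (total and each question) obtained at baseline will be compared between A+B vs C+D arm".
- A raw-score comparison after surgery: "BPI score (total and each question) obtained at postoperative day 2 will be compared between A+B vs C+D arm", with the same sentence for Day 4.
- The test: "Student t-test will be used. P value 0.05 will be used to determine significance".
- The conditional rule: "If BPI score at baseline is imbalanced between arms, change of BPI score (from baseline to postoperative day 2, 4) will be compared".

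The population is given as "Patient who undergo surgery and complete BPI". The row sets no threshold for imbalance. It does not say whether the rule works on the total or question by question, or whether the change-score result takes the place of the raw comparison or stands beside it. Day 2 and Day 4 BPI-K are secondary objectives D and E.

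**The concern.** The method depends on a feature of the data that the protocol leaves undefined, and neither of the two analyses it offers uses the baseline well. The raw-score t-test ignores it. The change score uses it with a fixed coefficient of 1, whatever the actual relation between preoperative pain and acute postoperative pain. The significance comparison at baseline tests a hypothesis that randomization already makes true, so it is a poor basis for choosing an analysis.

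At stake is the pain comparison between sutures. The protocol lists increased pain among the potential risks of the barbed suture, so the result will be read for safety as well as benefit. If the rule fires, the reader gets a comparison tilted by the chance difference that set it off. If it does not fire, the reader gets a less precise comparison than the collected data allow. Because the protocol itself names the test, the scale and the rule, this is not a detail left open for an analysis plan.

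**Working it through.** **Patients per arm.** The protocol states no SD, correlation or power for BPI-K, so n is taken from the primary design: "Alpha 0.05 (one-sided), power 0.8, drop-out rate 0.06, each arm (A+B vs C+D): 87 patients". That figure reproduces with the arcsine formula for 0.13 versus 0.03:

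- h = 2·asin(√0.13) − 2·asin(√0.03)
- n = 2(z₀.₉₅ + z₀.₈₀)²/h² = 81.5 per arm
- 81.5/0.94 = 86.7, i.e. 87 per arm

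After 6% dropout, 87 × 0.94 = 81.8, so 81 per arm is used below.

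**Bias given a baseline difference.** Let D be the chance baseline difference between arms, r the correlation of baseline with postoperative score, k the ratio of baseline SD to postoperative SD, and b = r/k the slope of postoperative on baseline score. With no treatment effect, the expected difference between arms given D is:

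- raw score: b·D
- change score: (b − 1)·D
- ANCOVA: 0

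The change score is unbiased given D only if b = 1. It over-corrects when b < 1 and under-corrects when b > 1. When b < 0.5 it lies further from zero than no adjustment at all.

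**Simulation.** Assumptions, none of them in the protocol: bivariate normal scores, equal SDs (k = 1), imbalance meaning baseline p<0.05, two-sided 0.05, change scores replacing raw scores when the rule fires, and 200,000 trials per setting. The rule fires in about 5% of trials. Rejection rates among triggered null trials, and overall type I error of the rule:

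| r | Change score, triggered | Raw score, triggered | ANCOVA, triggered | Rule, overall |
|---|---|---|---|---|
| 0.1 | 30% | 5% | 5% | 0.062 |
| 0.2 | 28% | 7% | 5% | 0.060 |
| 0.3 | 25% | 9% | 5% | 0.058 |
| 0.5 | 18% | 18% | 5% | 0.051 |
| 0.7 | 13% | 32% | 5% | 0.040 |

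If imbalance means p<0.20, the overall error at r = 0.2 is 0.068.

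**Unequal SDs.** At r = 0.3 the change-score rejection rate among triggered null trials is about 24% for k = 1, 15% for k = 0.75 and 8% for k = 0.5; the overall error is 0.056, 0.053 and 0.048. Over k = 0.5 to 1.25 and r = 0.1 to 0.7 the triggered rate runs from about 4% to about 40%.

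**Precision.** Relative to the raw-score t-test, ANCOVA has variance 1 − r², so the raw-score test forgoes a reduction of r²: 0.3² = 9%, 0.5² = 25%. Power at an assumed difference of 0.4 SD (k = 1):

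| r | Protocol's rule | ANCOVA |
|---|---|---|
| 0.1 | 0.71 | 0.72 |
| 0.2 | 0.71 | 0.73 |
| 0.3 | 0.71 | 0.75 |
| 0.5 | 0.72 | 0.83 |
| 0.7 | 0.73 | 0.94 |

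**The case against.** The rule is prespecified and is triggered by baseline, not by outcome. The endpoints are two of ten secondary objectives. If preoperative and acute postoperative pain are weakly correlated, the raw-score t-test loses little: 1% of variance at r = 0.1 and 9% at r = 0.3. All of that stands, and it limits the weight of the point.

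Three stronger readings are tempting and are not supported.

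- A reader might infer that the change score costs a fixed 54% in variance against ANCOVA. At r = 0.3 with equal SDs, 2(1 − 0.3)/(1 − 0.3²) = 1.40/0.91 = 1.54. The protocol gives no SDs. In general the ratio is (1 + k² − 2rk)/(1 − r²), which at r = 0.3 is 1.04 for k = 0.5, 1.22 for k = 0.75 and 1.99 for k = 1.25. It is also an unconditional variance, whereas the harm when the rule fires is bias.
- A reader might infer that the change score certainly displaces the raw comparison, so that the result not shown can never be known. The row does not say so. The covariate rule under Data Analysis and Statistical Analysis Methods adds the multivariate analysis to the univariate one. It does not name BPI-K, but it makes an additive reading possible. On that reading both results appear, and the protocol still does not say which one counts.
- A reader might infer that the overall false-positive rate is seriously inflated. In the settings examined it is not: about 0.04 to 0.07.

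What remains does not depend on these readings: the trigger is undefined, the correction is right only at a slope of 1, and a collected baseline goes unused in the default test.

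**Conclusion.** The point holds, at moderate weight. When the rule fires, the change-score comparison is biased unless the slope happens to be 1: about 13% to 30% false positives with equal SDs, and about 4% to 40% over SD ratios of 0.5 to 1.25, against about 5% for ANCOVA. In the roughly 95% of trials where it would not fire under a p<0.05 trigger, the cost is lost precision of r². The direction of the argument needs no assumption beyond randomization and a slope other than 1. The sizes rest on assumed correlation, SD ratio, normality, threshold and 81 per arm; the power figures also assume a 0.4 SD effect. The primary hernia analysis and the sample size of 174 are unaffected.

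**What to change.** Rewrite the BPI-K row: compare Day 2 and Day 4 scores between A+B and C+D by ANCOVA, with suture group as the factor and baseline BPI-K as covariate, whatever the baseline balance. Include the stratification factors from the randomization section (BMI group, surgery indication, and institution if numbers per site allow). Apply the same model to the total and to each question. Delete the baseline significance test and the change-score rule; baseline scores can still be described by arm.

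The cost is wording. Baseline BPI-K is already collected, so no new data or patients are needed. The one addition is a simple stated way of handling patients with a missing baseline form.
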